#### Secondary outcome

Self-efficacy, risk perception, outcome expectancy, socio-economic status and social support will be measured to assess the ability of these variables in predicting adherence

### Participant timeline {13}

The participant timeline is found in Table 3.

**Table 3 Tab3:** Schedule of assessment

Assessment	Baseline T0	Pre-treatment T1	3 months T2	6 months T3	18 months T4	36 months T5
Questionnaires						
Epworth Sleepiness Scale (ESS)	X			X		
Self-Efficacy Measure for Sleep Apnea	X		X	X		
(SEMSA)				X		
Pittsburgh Sleep Quality Index (PSQI)	X			X		
EQ-5D	X					
Socio-Economic Questionnaire	X					
Social Support Questionnaire	X					
Age	X					
Gender	X					
Body mass index (BMI)	X					
Neck circumference	X					
Objective measure of adherence			X	X	X	X
Subjective measure of adherence			X	X	X	X
One-to-one interviews				X		

### Study scheme diagram

The study scheme diagram is found in Fig. 1.

**Fig. 1 Fig1:**
[figure not shown]
Study Flow diagram

### Sample size {14}

A minimum sample size of 56 patients distributed in two groups is proposed for given α (0.01) and power (0.9), for 2 randomly assigned groups, intervention care (*n* = 28), standard care group (*n* = 28). Finally, assuming a maximum of 15% dropout, a total number of 64 patients is required.

### Recruitment {15}

As part of the routine care for patients presenting with sleep disordered breathing, they are all diagnosed with OSA, on the basis of an overnight sleep study, performed in sleep clinics. Patients requiring mandibular advancement appliance (MAA) therapy are then referred to specific dental sleep clinics for treatment, as part of a multi-disciplinary approach to care. We plan to recruit potential patients, with a confirmed diagnosis of OSA, that are specifically referred for MAA therapy to Barts’ Health NHS Trust.

## Assignment of interventions: allocation

### Sequence generation {16a}

A simple computer-generated randomisation method will be performed using a restricted (10-number block) random number sequence (www.graphpad.com/quickcalcs/randomn2.cfm) to ensure equivalence of numbers in each group. Participants will be stratified by OSA severity. In every 10-number block from the random table, the sequence will be checked to ensure the even numbers are equal to the odd numbers. Each number in the random table will be given a study number and assigned into one of the study groups.

### Concealment mechanism {16b}

A table for the allocation of the participants in the study will be composed and kept in a sealed opaque envelope by the CI.

All the documents related to the randomisation, and allocation sequence generation will be kept in a box in a locked cabinet away from the clinical environments in the CI’s office.

### Implementation {16c}

Research student ([name])

## Assignment of interventions: Blinding

### Who will be blinded {17a}

Only the research student (HT) and CI will have access to the Master file and patient allocation. Patients will be anonymised and allocated a unique study number and the data then blinded to the statistician, for analysis.

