### Trial design {8}

This study is a single-centre, superiority, two-arm, parallel-group, individually randomised clinical trial, with 1:1 allocation, designed to test the effectiveness of stage-matched intervention in enhancing patient adherence to MAA therapy in patients with OSA. In addition, we plan to recruit patients with a confirmed OSA diagnosis, specifically referred for MAA therapy from secondary care.

Ethical approval was obtained from the Greater Manchester West Research ethics committee (REC ref: 19/LO/0972 and 19/NW/0391). Patients meeting the eligibility criteria will be provided with a patient information leaflet explaining the whole study. Interested patients will be asked to sign the informed consent, after which they will be randomly assigned into two groups- intervention care (IC) and standardised care (SC). Only the investigator and chief investigator (CI) will be aware of the participant’s allocation.

Participants will be provided with a sleep diary (Additional file 1) to record their hours of sleep and MAA wear-time, which will give a subjective record of the adherence (duration of usage of MAA). The TheraMon®, a micro-sensor included in the MAA design, will be used for the objective documentation of MAA adherence. TheraMon® calculates the actual wear time by measuring temperature every 15 min and then transforms this information into wear time when the temperature ranges between two specific values. In the present study, this range is defined as 28 °C to 38 °C, which includes the vast majority of intraoral temperature values observed in an individual under normal conditions.

At baseline (T0), part of the routine clinical subject demographics to be collected will include age, gender, body mass index (BMI), and neck circumference. The AHI will also be recorded during the initial screening. Following an oral examination, upper and lower alginate impressions will be taken along with the participant's bite. In addition, participants will be asked to complete the following questionnaires at T (0):
Epworth Sleepiness Scale (ESS)Self-efficacy measure for sleep apnoea (SEMSA) modified for oral appliancePittsburgh Sleep Quality Index (PSQI)EuroQol-5 Dimension (EQ-5D)Socio-economic position questionnaireSocial support scale

The above questionnaires will provide information concerning the participant’s daytime sleepiness, personality, quality of sleep, health-related quality of life, socio-economic status and social support, respectively.

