### Who will take informed consent? {26a}

In line with standard care, patients will be provided information regarding the study via a Participant Information sheet and what will happen to them if they agree to participate. Once the patients have agreed to participate, the research student (HT) will take written informed consent from the participants.

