### Composition of the data monitoring committee, its role and reporting structure {21a}

The data recorded in this study will be stored securely both physically and electronically. The data will be analyzed in the Queen Mary, University of London by the CI of the research student. The data will be password protected and the only the CI and the research student will have full access. The personal data of the participants will be securely held within the research facilities at the Queen Mary, University of London, by the chief investigator.

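### Allocation concealment is not protected as written, and the article contradicts itself on whether the analyst is blinded

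*Protocol article*

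**What the plan says.** The relevant statements are spread over several sections of the protocol article.

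- **Consent {26a}:** the research student "will take written informed consent from the participants".
- **Implementation {16c}:** the only entry is "Research student".
- **Blinding {17a}:** the research student and the CI "will have access to the Master file and patient allocation". The same item says that the data are blinded to the statistician for analysis.
- **Concealment {16b}:** "A table for the allocation of the participants in the study will be composed and kept in a sealed opaque envelope by the CI". The randomisation documents stay in a locked cabinet in the CI's office, away from the clinic.
- **Sequence generation {16a}:** a "restricted (10-number block) random number sequence", with stratification by OSA severity. The article does not say whether each stratum has its own list.
- **Trial design {8}:** randomisation follows signed consent, and "Only the investigator and chief investigator (CI) will be aware of the participant’s allocation".
- **Data monitoring committee {21a}:** "The data will be analyzed in the Queen Mary, University of London by the CI of the research student". Only those two have full access to the data.

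**The concern.** Concealment means that whoever decides if and when a patient enters the trial cannot foresee that patient's arm. Here one person consents, allocates and has access to the allocation file.

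The outcome is hours of appliance use, a behaviour. The Background names intention, self-efficacy and outcome expectations among the determinants of adherence, and a recruiter may form an impression of these at the consent visit. If the next arm can be foreseen, timing or selecting patients by apparent motivation, even unknowingly, would put different kinds of patient in the two arms. The sensor measures use objectively but cannot repair that imbalance, and later analysis cannot reliably remove it. The planned groups are small, at 28 each (Sample size {14}).

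Analyst blinding is a separate matter. Assessing the aims of the study leaves the form of the adherence regressions to be settled after the data trends have been seen, so it matters whether the person choosing knows the arms.

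**Working it through.** The article gives no figure to reproduce. The check has three parts.

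**1. Roles and access**

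| Function | Who | Item |
|---|---|---|
| Takes consent | Research student | {26a} |
| Implements allocation | Research student | {16c} |
| Access to master file and allocation | Research student and CI | {17a} |
| Holds the sealed table | CI | {16b} |

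The first three functions meet in one person. The fourth separates that person from the list only while the envelope is closed. As described, one envelope holds the whole table, so reading the first assignment also exposes the rest. No step is described that releases one assignment at a time.

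**2. Predictability if only past assignments are seen**

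Inputs: block size 10 {16a} and 1:1 allocation {8}, so m = 5 per arm in each block. Assume the enroller knows all earlier assignments in the block, always guesses the arm that is behind, and picks at random when the arms are level.

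- Expected correct guesses per block = m + ½ × (2^(2m) / C(2m, m) − 1) = 5 + ½ × (1024/252 − 1) = 5 + ½ × 3.06 = 6.53 of 10, or about 65%.
- Expected assignments known with certainty (one arm already full) = 2 × m/(m + 1) = 5/6 + 5/6 = 1.67 of 10, or about 17%.

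A simulation of 100,000 blocks of 10 gave 65.3% correct and 1.67 certain per block, which agrees. With no information on the sequence, the values are 50% and 0%.

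For the planned 56 patients this is about 56 × 0.653 = 36.6 correct guesses against 28 by chance, and up to about 56 × 0.167 = 9.3 assignments known in advance. These figures average over complete blocks; unfinished blocks lower them. If blocks are kept per severity stratum, they apply within each stratum.

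The two figures rest on different knowledge. The 17% needs the block size. The 65% needs only the past assignments, because the arms return to balance at the end of every block.

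**3. Who analyses**

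- {17a}: a statistician to whom the data are blinded.
- Data management {19}: data are transferred for analysis in anonymised form, which fits a separate statistician. The same item limits access to the CI and the research student.
- {21a}: the analysis is by the CI of, or perhaps or, the research student.

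On either reading of {21a}, the analyst is someone whom {17a} lists as having the allocation. The two items cannot both be followed.

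**The case against.** The case on the other side has real substance.

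- **The list is guarded.** The CI holds it in an opaque envelope, in a locked cabinet away from the clinic, and only the student is named as taking consent. Randomisation already follows consent. This stands as mitigation.
- **The access statement sits under blinding, not concealment.** It may mean only allocations already made. That is a fair reading, but the text sets no such limit, and part 2 of the check shows that prediction remains possible under it.
- **The guessing figures need an enroller who tracks assignments and predicts.** They show what is possible, not what was done.
- **The {21a} sentence may be a slip.** It closely resembles the storage text in Data management {19}, where the verb is accessed rather than analysed. This is plausible, but the conflict with {17a} still needs a correction.
- **The article condenses a full protocol.** Per-patient envelopes or release steps may be described there. Their absence alone would be no finding. The point rests on what the article does state: the combined roles, the unrestricted access, the single table and the fixed block.

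A reader might go further and infer that concealment has failed, that every assignment is foreseeable, or that the analysis is unblinded. The documents do not support this. Full foreseeability requires the student to see the unused part of the table, which no section states, and {17a} explicitly provides for a blinded statistician.

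**Conclusion.** The point holds in two limited parts.

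1. **Concealment is not protected as written.** One person consents, allocates and has access to the allocation without a stated limit, and a single table in a single envelope cannot hide later assignments once opened. On the milder reading, with only past assignments known, about 65% of assignments can be guessed and about 17% are certain, against 50% and 0%. This assumes complete blocks of 10 and an enroller who keeps track. The resulting bias in the adherence comparison cannot be sized from the documents.
2. **The article contradicts itself on the analyst.** {17a} and {21a} must be reconciled. This is a conflict of wording, not proof that the analysis will be unblinded.

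**What to change.** - Keep the list with the CI, or with another existing person, provided that the holder neither enrols nor analyses. The analysing statistician should not hold it, since that would unblind the analysis.
- Replace the single table with one sequentially numbered, opaque, sealed envelope per participant, opened only after consent and T0 data are recorded.
- For any remaining participants, use undisclosed, randomly varied block sizes within OSA-severity strata. This removes most of the certainty but not the guessing advantage, and short blocks would increase that advantage: by the formula above, blocks of 4 give 2 + ½ × (16/6 − 1) = 2.83 of 4, or 71%. Very short blocks are best avoided.
- State in {17a} that the student's access covers only assignments already made.
- Amend {21a} to agree with {17a}: the blinded statistician analyses coded arms until the primary analysis is fixed.

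Trial status gives recruitment from December 2019 to about September 2021. If it has ended, the allocation steps can no longer be changed. The team should then document how each assignment was actually released and by whom, and secure the coded-arm analysis.

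The cost is a protocol amendment, a new envelope set for any remaining participants and a small handling step at each randomisation, using people already on the study.

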### Procedure for unblinding if needed {17b}

Not applicable

## Data collection and management

### Plans for assessment and collection of outcomes {18a}

Questionnaire responsesMandibular advancement appliance with an in-built sensor will be used to collect objectively measured adherence

### Plans to promote participant retention and complete follow-up {18b}

Data concerning adherence will be retained.

### Data management {19}

The data recorded in this study will be stored securely both physically and electronically. The data will be accessed at the Queen Mary University of London by the CI and research student only and will be password protected. The personal data of the participants will be securely held within the research facilities at the Queen Mary University of London, by the chief investigator. Data transfer for analysis will be undertaken in an anonymised form, using unique ID numbers and password-protected access.

### Confidentiality {27}

Information related to participants will be kept confidential and managed in accordance with the Data Protection Act, NHS Caldecott Principles, The Research Governance Framework for Health and Social Care, and the conditions of Research Ethics Committee Approval.

### Plans for collection, laboratory evaluation and storage of biological specimens for genetic or molecular analysis in this trial/future use {33}

Not applicable

## Statistical methods

### Statistical methods for primary and secondary outcomes {20a}

Both objective and subjective data of adherence i.e. duration of the usage of the appliance will be collected at 3, 6, 18 and 36 months will be analysed to assess the effectiveness of Intervention care in comparison with standardised care.

Comparison of pre- and post-treatment scores of ESS, SEMSA, PSQI, and EQ-5D, for both the groups, will aid in identifying significant differences in terms of improvement.

Statistically, evaluate the ability of the variables -self-efficacy, risk perception, outcome expectancy, social support and socio-economic position, to predict patient adherence at 3, 6, 18 and 36 months.

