##### Secondary objectives

The secondary outcomes are as follows:
To identify the psychosocial and socio-economic indicators enhancing adherence of MAA in patients with OSA.Use of the indicators to develop a psychological and socio-economic predictor model.

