#### Secondary endpoint

Self-efficacy, risk perception, outcome expectancy, socio-economic status and social support will be measured to assess the ability of these variables in predicting adherence.

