#### Assessing the aims of the study

In order to assess the aims of the study, we will test each of the repeated measures first by themselves using a repeated measures ANOVA controlling for groups:
Adherence – reported, times 3, 6, 18, 36 difference 3–6, 6–18, 18–36Adherence – objective, times 3, 6, 18, 36 difference 3–6, 6–18, 18–36ESS, time 6, difference 0–6PSQI, time 6, difference 0–6EQ5D, time 6, difference 0–6Risk perception, times 3, 6, difference 0–3, 0–6, 3–6Outcome expectancy, times 3, 6, difference 0–3, 0–6, 3–6Self-efficacy, times 3, 6, difference 0–3, difference 0–6, 3–6

Once we understand the trends in the data, we can construct multiple regressions for Adherence variables. These can be the final measures from time 6 or the differences between them and previous times, 0 or 3. In these models, we will use the Psychosocial variables and socio-economic as predictors, beyond the group classification.

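### ESS, PSQI and EQ-5D are tested but not declared as outcomes, and for them and SEMSA no between-arm contrast is named, so a pre-post change could be reported as an intervention effect

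*Protocol article*

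**What the plan says.** **Outcome definitions.** In the Protocol article, the Secondary outcome under Outcomes {12} is "Self-efficacy, risk perception, outcome expectancy, socio-economic status and social support will be measured to assess the ability of these variables in predicting adherence". The Secondary endpoint section uses the same words. The Secondary objectives agree in purpose: "To identify the psychosocial and socio-economic indicators enhancing adherence of MAA in patients with OSA", followed by a predictor model. None of these sections mentions ESS, PSQI or EQ-5D.

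**Statistical methods {20a}.** This section has three parts:
- Adherence is compared between intervention care and standardised care.
- For the scales, it plans "Comparison of pre- and post-treatment scores of ESS, SEMSA, PSQI, and EQ-5D, for both the groups, will aid in identifying significant differences in terms of" patients' improvement.
- The five declared variables are then assessed as predictors of adherence.

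**Assessing the aims of the study.** Here "we will test each of the repeated measures first by themselves using a repeated measures ANOVA controlling for groups". Besides reported and objective adherence, the list holds ESS, PSQI and EQ-5D (month 6 and the change from 0 to 6). It also holds risk perception, outcome expectancy and self-efficacy, the constructs that the abstract ties to SEMSA (months 3 and 6 and the changes 0–3, 0–6 and 3–6). Regressions of adherence on the psychosocial and socio-economic variables follow.

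**The concern.** Two things do not fit together. First, three scales are tested under a heading for primary and secondary outcomes, and again as part of assessing the study's aims, but no aim, endpoint or outcome section covers them. The three SEMSA constructs are declared only as predictors of adherence, yet they are also tested as responses.

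Second, the comparison that would show an effect of the intervention on these scales is not named. A pre-post comparison in each arm, or a time effect in a model that merely adjusts for arm, measures what happens to patients who are fitted with the appliance. Both arms are fitted with it (Explanation for the choice of comparators {6b}). The Background itself says that the appliance reduces daytime sleepiness and cites improved quality of life with it. Shared improvement is therefore expected without any effect of the behavioural intervention.

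At stake are the claims beyond wear time: whether the intervention also improves sleepiness, sleep quality, quality of life and self-efficacy. The primary outcome is not affected.

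**Working it through.** **Step 1: the sections side by side.**

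| Variable | Secondary endpoint; Secondary outcome | Statistical methods {20a} | Assessing the aims of the study |
|---|---|---|---|
| ESS, PSQI, EQ-5D | not listed | pre/post scores, both groups | repeated measures ANOVA, group controlled for |
| Self-efficacy, risk perception, outcome expectancy (SEMSA) | predictors of adherence | pre/post scores, and predictors | repeated measures ANOVA as responses, then predictors |
| Social support, socio-economic status | predictors of adherence | predictors | predictors in the regressions |
| Adherence | primary outcome | IC compared with SC | repeated measures ANOVA, group controlled for |

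The five predictors appear in every column. The additions are ESS, PSQI and EQ-5D, and the second role given to the SEMSA constructs. Only the adherence row of {20a} states an IC-versus-SC comparison.

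**Step 2: what a pre-post reading would cost.** There is no figure in the plan to reproduce, so this is an illustration.

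Inputs:
- n = 28 per arm and α = 0.01, from Sample size {14}. Sidedness is not given; two-sided is assumed.
- α = 0.05 is shown for comparison only; the protocol does not state it.
- d = mean change divided by the SD of within-person change, the same true value in both arms (no intervention effect). The values of d are assumptions.

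For one arm, a paired t-test shows significant improvement with probability

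p = P(T > t(1−α/2; 27)), where T is noncentral t with 27 degrees of freedom and noncentrality d√28.

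The arms are independent, so P(IC significant, SC not) = p(1−p).

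| d | p at 0.01 | p(1−p) at 0.01 | p at 0.05 | p(1−p) at 0.05 |
|---|---|---|---|---|
| 0 | 0.005 | 0.5% | 0.025 | 2.4% |
| 0.2 | 0.057 | 5.4% | 0.174 | 14.4% |
| 0.3 | 0.139 | 12.0% | 0.334 | 22.2% |
| 0.4 | 0.278 | 20.1% | 0.532 | 24.9% |
| 0.5 | 0.463 | 24.9% | 0.723 | 20.0% |
| 0.6 | 0.657 | 22.5% | 0.864 | 11.7% |
| 0.8 | 0.918 | 7.5% | 0.983 | 1.7% |

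Example: for d = 0.5 at 0.01, 0.463 × (1 − 0.463) = 0.249.

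**Step 3: the comparator.** A two-sided between-arm test with no true effect falsely favours IC with probability α/2, which is 0.5% at 0.01 and 2.5% at 0.05, whatever change the arms share. With d = 0 the two routes nearly agree, so the excess comes from the shared improvement. Because p(1−p) cannot exceed 0.25, 25% per scale is the ceiling for any assumed d.

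**The case against.** The best defence is that {20a} only introduces the analysis and the later section specifies it. That section puts group in the model and lists no paired test. The pre/post sentence can also be read as comparing improvement between the groups. Which model term carries the test is detail that an analysis plan often settles.

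Much of this stands. The within-arm reading is permitted by the wording, not prescribed. But an analysis plan would not remove the mismatch between the outcome sections and the analyses in this document, and the same section shows that an IC-versus-SC comparison could have been stated in a few words.

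Some stronger readings are tempting, and the document does not support them:
- *The statistical section replaces the declared secondary endpoint.* It does not: {20a} repeats all five predictors, and the SEMSA constructs are in both lists.
- *Baseline covariates are treated as outcomes.* Table 3 (Participant timeline {13}) does schedule social support and socio-economic status at baseline only, but the stated purpose is prediction, and nothing plans to test them as results of treatment. This is a matter of labels.
- *The error is 40 to 50% per scale.* That is the peak range of 2p(1−p), which counts results favouring either arm. A false claim for the intervention needs IC only, which is half.
- *The listed values and change scores are a family of 21 tests (3 × 2 + 3 × 5) with a very high overall error.* Many of these contrasts are combinations of one another, the plan names one repeated measures ANOVA per measure, and it does not say that each contrast supports a claim.

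It is also fair that no objective concerns an intervention effect on ESS, PSQI or EQ-5D. Calling them exploratory would therefore close the gap as well as calling them secondary.

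**Conclusion.** The point holds in a limited form. ESS, PSQI and EQ-5D are tested without a declared status, the SEMSA constructs change role between sections, and no IC-versus-SC contrast is named for any of these scales. A pre-post improvement, which the wording allows as the basis for a finding, is not evidence of an intervention effect when both arms receive the appliance.

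If benefit were inferred from significance in IC alone, the false-claim rate per scale would be 12% to 25% at two-sided 0.01 for d from 0.3 to 0.6, and 7.5% at d = 0.8. A between-arm test would give 0.5%. These figures rest on 28 analysed per arm, equal true improvement in both arms, the assumed d and that rule of inference. They show what the wording leaves open; they do not predict what the investigators will do. The change should be made, but it does not bear on the primary outcome.

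**What to change.** 1. In Statistical methods {20a}, replace the pre/post sentence with: *The intervention effect on ESS, PSQI, EQ-5D and each SEMSA scale is the between-arm difference (IC minus SC) at 6 months, adjusted for the baseline score, with its confidence interval. Within-arm changes are descriptive only.*
2. In Assessing the aims of the study, name that group contrast, or the group-by-time term, as the test for these scales.
3. In Secondary endpoint and Secondary outcome, state whether ESS, PSQI, EQ-5D and SEMSA are secondary or exploratory outcomes, separately from the analysis of predictors of adherence.

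No visit or data item is added: Trial design {8} and Table 2 already schedule these questionnaires at baseline and 6 months. The cost is a protocol amendment to wording, communicated as {25} requires, after a recruitment start in December 2019. Within-arm improvements could then no longer support a claim of benefit.
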